## Abstract

**Background:**

Obesity, eating disorders and unhealthy weight-loss practices have been associated with diminished growth in adolescents worldwide. Interventions that address relevant behavioural dimensions have been lacking in Malaysia. This paper describes the protocol of an integrated health education intervention namely ‘Eat Right, Be Positive About Your Body and Live Actively’ (EPaL), a primary prevention which aimed to promote healthy lifestyle in preventing overweight and disordered eating among secondary school adolescents aged 13–14 years old.

**Methods/Design:**

Following quasi-experimental design, the intervention is conducted in two secondary schools located in the district of Hulu Langat, Selangor, Malaysia. Adolescents aged 13–14 years will be included in the study. A peer-education strategy is adopted to convey knowledge and teach skills relevant to achieving a healthy lifestyle. The intervention mainly promoted: healthy eating, positive body image and active lifestyle. The following parameters will be assessed: body weight, disordered eating status, stages of change (for healthy diet, breakfast, food portion size, screen viewing and physical activity), body image, health-related quality of life, self-esteem, eating and physical activity behaviours; and knowledge, attitude and practice towards a healthy lifestyle. Assessment will be conducted at three time points: baseline, post-intervention and 3-month follow-up.

**Discussion:**

It is hypothesized that EPaL intervention will contribute in preventing overweight and disordered eating by giving the positive effects on body weight status, healthy lifestyle behaviour, as well as health-related quality of life of peer educators and participants. It may serve as a model for similar future interventions designed for the Malaysian community, specifically adolescents.

**Trial registration:**

UMIN Clinical Trial Registration UMIN000024349 (Date of registration: 11th. October 2016, retrospectively registered).

## Background

Globalisation, urbanisation and economic development in the past century have had a negative impact on eating habits and exercise in both developed and developing nations. This impact is evident in modern adolescents’ eating and physical activity regimens. In Malaysia, adolescents, individuals aged 10–19 years, make up a population of 5.5 million i.e., 18.9 % of the entire Malaysian population [1].

At the age of adolescence, major physical, psychological and social changes occur. For instance, this stage of development is the second chance of catch-up growth before entering adulthood. Inadequate intake of carbohydrates, proteins, fat, vitamins and/or minerals has been shown to have severe consequences on growth during this stage, and is associated with delayed onset of puberty [2]. This is because nutritive demands of adolescence are only second to infancy. Excessive food intake, however, has also been shown to have detrimental effects on adolescents’ health, such as increasing their susceptibility to diseases and precipitating diabetes, heart disease and hypertension [3].

Overweight and obesity are major public health issues in both developed and developing countries. Between 1980 and 2013, the prevalence of overweight and obesity in developed countries remarkably increased from 16.9 and 16.2 % to 23.8 and 22.6 % in male and female adolescents respectively; whereas in developing countries, a whopping 9.8 % increase in the number of overweight and obese adolescents was observed around the same period of time [4].

In Malaysia, high percentages of overweight and obese adolescents, as well as adolescents suffering from disordered eating have been reported. According to the National Health and Morbidity Survey (NHMS), the prevalence of obesity in Malaysian adolescents increased dramatically between 2011 and 2015 from as low as 6.1 % [5] to 11.9 % [6]. Alarmingly, estimates from a separate nationwide study showed that as of 2015, 14.2 % of Malaysian adolescents aged 12–19 were overweight, while 10.1 % were rather obese [7].

Disordered eating refers to unhealthy eating and weight related behaviours and attitudes that are of medical and/or psychological concern but cannot be labelled as eating disorders [8]. In Malaysia, disordered eating is rampant. Approximately 22.3 % of female adolescents in the state of Kelantan [9] and 27.8 % of adolescents in the state of Pahang were found to be suffering from disordered eating [10]. Overweight and obese adolescents were shown to be significantly more prone to disordered eating behaviours than non-overweight, non-obese adolescents of similar age groups [7]. Such behaviours are associated with higher risk of non-communicable and chronic diseases in adulthood. Hence, immediate action to prevent overweight and disordered eating in Malaysia seems to be highly warranted. Obesity and disordered eating share a number of risk factors, such as unhealthy eating attitudes, body dissatisfaction and weight-related teasing among adolescents [11]. Hence, tackling obesity and disordered eating may be achieved using the same approach.

Poor body image can result in negative effects on a child’s or an adolescent’s weight. The physiological changes that happen to the body during adolescence contribute to negative body image [12, 13] and are associated with a multitude of weight-related issues, including obesity, disordered eating, binge eating and extreme weight-control practices [14]. Hence, to be effective, interventions aiming to decrease the incidence of obesity and disordered eating among adolescents should promote positive body image, eating habits and physical activity [15].

This study sought to effect positive changes in the prevalence of overweight and disordered eating in adolescents aged 13–14 years in Form 1 and 2 of secondary school. Most Malaysian adolescents experience puberty and an increase in body fat around this age, which is coincidently the age at which students frequently build new friendships and establish new group norms. This often contributes to body dissatisfaction and unhealthy dietary choices, such as extreme dieting and binging [16, 17], leading to poor overall health status [16]. School students aged 12–15 years are an ideal group to study the effects of universal prevention approaches as the majority of the social, psychological and environmental risk factors that can trigger eating disorders and lead to overweight are most prominent [18]. Therefore, the present peer-group intervention was designed to drive students during this stage of early adolescence to develop attitudes and behaviours that would rather nurture healthy lifestyles.

Achieving nutritional goals, promoting physical activity and positive body image have become the pillars of both obesity and eating disorder prevention programmes. Integrating obesity prevention approaches into behavioural interventions designed to tackle eating disorders has been shown to be more advantageous than separate programmes as it lacks mixed messages and represents a strategy that is more time- and cost-effective [19]. Several integrated interventions implemented around the world have been shown to be successful in the past, such as MABIC [20] and New Moves [21]. New Moves utilised integrated concepts and teaching strategies adopted from both obesity and eating disorder prevention programmes. It promoted physical activity and improved eating patterns in female adolescents by altering negative body image conventions and effecting positive behavioural changes. Another integrated intervention, Healthy Buddies, achieved similar goals in elementary school students, but rather by using a peer-led approach [22].

Healthy Lifestyle in Children (HELIC) [23], Healthy Kids Programme [24], Body Image Education Package [25] and the Malaysian Childhood Obesity Treatment Trial (MASCOT) [26] are a few of many school-based interventions that had been implemented in Malaysia. However, most of these interventions have rather been stand-alone programmes in the sense that they focused either on the prevention of obesity or the prevention of disordered eating. As far as our knowledge goes, Malaysia has not seen a comprehensive intervention programme that promotes all three components of a healthy life: healthy eating, active lifestyle and positive body image.

‘Eat Right, Be Positive About Your Body and Live Actively’ (EPaL) is an integrated health education intervention, which developed to prevent overweight and disordered eating among Malaysian adolescents. This intervention was formulated with the understanding that obesity, disordered eating, and extreme weight loss practices were strongly correlated and shared the same risk factors. Hence, it delivered a coherent message while tackling a broad spectrum of eating- and weight-related health issues. Unlike Healthy Buddies, EPaL did not use a one-to-one approach [22], but rather involved training a group of adolescents to become peer educators who then led others to fully implement the intervention. It differed from MABIC as it stipulated that the trainees be adolescents rather than educators or health care providers, such as tutors, clinical psychologists and nurses [20].

This paper describes the protocol for an integrated health education intervention namely ‘Eat Right, Be Positive About Your Body and Live Actively’ (EPaL), a primary prevention which aimed to promote healthy lifestyle, which including healthy eating, positive body image and active lifestyle, in preventing overweight and disordered eating among first and second year secondary school adolescents. In the present work, adolescents were used to ascertain whether or not EPaL could serve as an effective tool to promote health in Malaysian adolescents and reduce the incidence of overweight and disordered eating. The intervention was developed by taking consideration on risk factors and cultural background of Malaysian population, which might be different from other countries. The risk factors of interest were determined beforehand by carrying out a wide survey amongst secondary school adolescents throughout Malaysia.

## Methods/Design

### Study design

EPaL is a school-based intervention programme targeting adolescents in the early years of secondary school. The present study adopted a quasi-experimental design, in which adolescents from one school were included in the intervention group, while those from another school served as the comparison group and were not subjected to the intervention until the end of the period of experimentation. Adolescents in the comparison group attended a standard physical and health education class at least once a week. As the study was concluded, they were allowed to receive EPaL modules and educational materials. A flowchart of the intervention is shown in Fig. 1.

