### Setting, recruitment and participants

Two schools were randomly selected in the district of Hulu Langat, the state of Selangor, Malaysia. One school will randomly chose to receive the intervention, while adolescents in the other served as the comparison group. Selection of the schools will be performed by means of a draw from a list of schools in Selangor, obtained from the website of the state’s Department of Education. Only schools that met the inclusion criteria (coeducational, multiracial, non-residential and non-religious) were included in the draw. Adolescents who were Form 1 or 2 students and 13–14 years old; and whose parents consented to the intervention met the criteria for inclusion in the study.

A seminar will be held for the parents and teachers of Form 1 and 2 students in which EPaL will be introduced. Parents and teachers were asked to promote the programme to the students. Recruited students were presented with the research’s information sheet and consent letters to be read and filled by them and their parents. Written consent letters were collected from participating adolescents and their parents prior to the intervention. Thereafter, the students were subjected to the EPaL intervention programme over the course of 16 weeks in their school. They were assessed in three points of assessments, which are prior to the intervention (baseline), after the final session of the programme (post-intervention) and 3 months thereafter (follow-up).

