### Sample size calculation

The sample size calculation was based on the differences between groups (overweight and obese; and non-overweight and non-obese) in the proportion of having disordered eating. The value was taken from the outcome of needs assessment study, which was conducted involving 9677 adolescents aged 12–19 years throughout Malaysia. Based on the study, the proportion of overweight and obese adolescents who were having disordered eating was 40.3 %, whereas the proportion of non-overweight and non-obese adolescents who were having disordered eating was 27.9 %. Assuming a power of 80 % and a level of significance of 5 %, we needed 234 participants for each intervention and comparison groups, respectively. The effect size for proportions was estimated by the differences in the arcsine transformations of the respective proportions. The medium effect size of 25.4 % was obtained.

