### Data analysis

Data will be analysed by using version 21 of the IBM SPSS Statistical software (IBM SPSS Statistics, Inc., Chicago, IL, USA). Depending on the distribution of the variable of interest, descriptive statistics of continuous data will be presented by using the mean and standard deviation, and the median and the inter-quartile range. Categorical data will be presented as frequencies and percentages. *T*-test will be used to detect differences between groups for continuous variables, while chi-square will be used to investigate possible correlations between categorical variables. The repeated measures analysis of variance (ANOVA) will be used to detect significant differences within the groups. The evaluation of the intervention will be based on an intention-to-treat analysis. Differences with *p*-values < 0.05 were considered significant.

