The present study has several strengths. It demonstrated the uniqueness of peer-led intervention approaches in promoting healthy lifestyle among Malaysian students. Advantages of the peer-led approach were highlighted in previous studies. Generally, peer educators testified that peer-led approach gave them a valuable opportunity for personal development and learning by build upon young people’s skills and abilities [56, 57]. It also resulted in greater improvement in healthy lifestyle practices [53].

This study also contributed educational modules, activity books and educational materials that could serve as references and teaching materials and which may be suitable for use by the Malaysian Ministry of Health, Malaysian Ministry of Education, NGOs, health professionals, schools and parents.

Yet, the present work has several limitations. For instance, randomisation was only performed when selecting the schools. The use of an experimental design that ensures randomisation while recruiting participants and assigning peer educators would be more favourable and may produce higher levels of confidence to term of the validity and causality of the programme’s effectiveness [58]. Nevertheless, the quasi-experimental design used in this study may have better mimicked a real-life situation. Quasi-experimental design allows researchers to study a phenomenon in a natural setting in real-time [59, 60]. Overall, the results of this study will add to the knowledge and evidence of the effectiveness of the health intervention. It may be useful as a model to develop future health and nutrition interventions for adolescents in Malaysia.

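### With one school per arm, the 80% power and the p-values of the between-group tests hold only if students in the same school are no more alike than students in different schools

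*Protocol article*

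**What the plan says.** Under Study design, the protocol article states that "adolescents from one school were included in the intervention group, while those from another school served as the comparison group". Under Setting, recruitment and participants, it adds "Two schools were randomly selected in the district of Hulu Langat, the state of Selangor, Malaysia", and then "One school will randomly chose to receive the intervention, while adolescents in the other served as the comparison group". The unit of allocation is therefore the school, with one per arm.

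Under Sample size calculation, the inputs are proportions with disordered eating of 40.3% and 27.9%, and the text reads "Assuming a power of 80 % and a level of significance of 5 %, we needed 234 participants" for each of the two groups, which makes 2 × 234 = 468 students. No ICC or design effect appears.

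Under Data analysis, a t-test "will be used to detect differences between groups for continuous variables, while chi-square will be used" for categorical ones. Repeated measures ANOVA is reserved for differences within the groups, and p < 0.05 counts as significant.

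The limitations paragraph of the Discussion concedes that "randomisation was only performed when selecting the schools". It mentions neither clustering nor the fact that each arm is a single school.

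**The concern.** Students in one school share intake, canteen, teachers and peer culture, so their outcomes tend to be correlated. When schools are allocated, the difference between arms contains the difference between schools. With several schools per arm, the spread among schools within an arm shows how large that component is. With one school per arm there is no such spread and nothing from which to estimate it.

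The t-test and chi-square ignore this component, so their standard errors are too small by an amount the trial cannot measure. A p-value below 0.05 may show only that two schools differ, or that they changed differently over the period. Every between-group test read as an effect of EPaL is affected. So is the claim of 80% power, and with it the intended reading of the results as evidence of effectiveness.

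**Working it through.** **Inputs from the protocol article.** One school per arm (Study design); 40.3% and 27.9%, power 80%, significance 5%, 234 per group (Sample size calculation). Two-sided testing is assumed because the article does not state it.

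**Input not in the article.** The ICC. I assume 0.005 to 0.05 and add 0.001 as a very small value.

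**Step 1: reproduce 234.** The article says it used arcsine-transformed proportions.

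- h = 2·asin(√0.403) − 2·asin(√0.279) = 0.2626
- n per group = 2·((1.960 + 0.842)/h)² = 227.7, so 228
- The pooled two-proportion formula gives 229. The article's own printed effect size of 0.254 gives 244.
- Power at 234 per group = Φ(h/√(2/234) − 1.960) = 81%

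The stated 234 is within 3% of 228 and 229. It is a calculation for independent individuals. Multiplying 228 by the design effect for ICC 0.005 shown below would more than double it, so no such factor was applied.

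**Step 2: effect of clustering with m = 234 students per school.**

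- Design effect: DE = 1 + (m − 1)·ICC = 1 + 233·ICC
- Effective number per arm: 234/DE
- True two-sided error of the nominal 5% test: 2·(1 − Φ(1.960/√DE))
- Power of a test corrected with a known ICC: Φ(h/√(2·DE/234) − 1.960)
- Factor by which an unadjusted confidence interval must widen: √DE

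| Assumed ICC | DE | Effective n per arm | True error of planned test | Power of corrected test | Interval factor |
|---|---|---|---|---|---|
| 0 | 1.00 | 234 | 5% | 81% | 1.00 |
| 0.001 | 1.23 | 190 | 7.8% | 73% | 1.11 |
| 0.005 | 2.17 | 108 | 18% | 49% | 1.47 |
| 0.01 | 3.33 | 70 | 28% | 34% | 1.82 |
| 0.02 | 5.66 | 41 | 41% | 22% | 2.38 |
| 0.05 | 12.65 | 18.5 | 58% | 12% | 3.56 |

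The error and power columns describe different tests. The error rate belongs to the unadjusted test that the article plans. The power belongs to a hypothetical corrected test. It is optimistic, because it treats the ICC as known.

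**Step 3: check by simulation.** Two schools of 234 students, school proportions drawn from a beta distribution with mean 34%, no intervention effect, 200,000 repetitions. The unadjusted chi-square rejected in 18.3%, 28.5%, 41.4% and 59.0% of runs at ICC 0.005, 0.01, 0.02 and 0.05. This agrees with the formula.

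**Step 4: can the two schools be rescued?**

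- Degrees of freedom for between-school variance = 2 schools − 2 arms = 0.
- Adding students does not help enough. As m grows, the effective number per arm approaches 1/ICC, which is 200, 100, 50 and 20 for ICC 0.005 to 0.05. All are below the 228 required.
- The random choice of which school receives EPaL does not help either. It has two possible outcomes, so a randomisation test cannot give a p-value below 1/2.

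**The case against.** The best counter-arguments are these.

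- **Baseline data.** All students are measured at baseline, after the programme and three months later. Comparing change between schools could remove stable differences such as intake. That is right as far as it goes, and it narrows the confounding. It does not remove differing time trends in the two schools, and Data analysis names no between-group comparison of change.
- **Within-group tests.** The repeated measures ANOVA concerns change inside one school, so between-school variance does not enter it. This stands: the criticism applies to the between-group tests. The within-group tests cannot by themselves show an intervention effect.
- **The ICC is assumed.** This also stands. Drawing both schools from one district, under common eligibility criteria, may lower the ICC, and the ICC for change may differ from that for a single time point. The upper-end figures are illustrative. The direction does not depend on the value, and even ICC 0.001 breaks the stated level.
- **The contrast.** The proportions 40.3% and 27.9% compare overweight or obese with other adolescents, not the trial arms. The power figures here therefore show the loss relative to the article's own calculation. They are not power for a stated EPaL effect. This is a separate weakness and does not repair the present one.
- **The limitation is admitted.** The article calls the design quasi-experimental and says that randomisation in recruiting students and assigning peer educators could give more confidence about causality. It does not say that the error rate and power fail, and it still expects the results to add to the evidence of effectiveness.
- **The article is condensed.** Design, sample size, tests and significance rule are all stated. No fuller analysis plan can recover a between-school variance from one school per arm.

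**Conclusion.** The concern holds. The sample size and the between-group tests treat 468 students as independent, although only two schools were allocated. The 5% level and 80% power are therefore conditional on ICC = 0, which the article neither states nor supports.

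Under an assumed ICC of 0.005 to 0.05, two-sided testing and 234 students in each school, the false-positive rate of the planned test is about 18% to 58%. A test corrected with a known ICC would have about 49% to 12% power for the article's two proportions. The exact size depends on the ICC. The confounding of school with intervention does not, and no analysis of these two schools alone can remove it. A two-school quasi-experiment is a legitimate choice. The error lies in attaching confirmatory error rates to it.

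**What to change.** Four changes, none of which needs new schools or students:

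1. **Sample size calculation:** state that 80% power applies only if ICC = 0, and add a table of power for ICC 0.005 to 0.05.
2. **Data analysis:** report between-school differences as estimates, with confidence intervals widened by √DE over the same ICC range (factors 1.47 to 3.56 at 234 per school). Label this a sensitivity analysis on an assumed ICC. Do not use the unadjusted p < 0.05 as evidence of effectiveness.
3. **Data analysis and limitations:** state that there is one school per arm, that school and intervention are confounded, and that the between-school variance cannot be estimated.
4. **Discussion:** limit the conclusion to feasibility or preliminary evidence.

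The cost is wording and one small table, plus weaker claims.

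A confirmatory test would need more schools. The number of students per school for k schools per arm is 227.7·(1 − ICC)/(k − 227.7·ICC). At ICC 0.01 and k = 4 this is 225.4/1.723, about 131 students per school, before any small-sample correction. That is a matter for a later trial.
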